### Statistical methods

Descriptive statistics, including means and standard deviations, will summarize the data. The Shapiro-Wilk test will assess data normality. Baseline characteristics will be summarized descriptively between groups. Repeated-measures ANOVA will be used to evaluate the group × time interaction effect as the primary indicator of intervention effectiveness (training vs. control; pre-test vs. post-test). Pairwise comparisons following significant interactions will be conducted with Bonferroni correction to control type I error. The five secondary outcome domains (cortical brain activity, lower-limb muscle activation, single-leg balance, muscle strength, and knee joint proprioception) will be interpreted as exploratory outcomes and hypothesis-generating findings. Partial eta squared will quantify effect sizes, interpreted as small (0.01), medium (0.06), or large (0.14). All analyses will be performed using SPSS version 27 with α = 0.05 and a 95% confidence level.

Given the modest sample size, supplementary analyses will be conducted. Baseline values will be reviewed descriptively, and if clinically meaningful baseline imbalance is observed, ANCOVA models adjusting for baseline values will be performed as sensitivity analyses. Missing data patterns will be assessed, and linear mixed models with appropriate covariance structures will be considered as sensitivity analyses to evaluate robustness under missing-at-random assumptions. Any meaningful discrepancy between supplementary analyses and the primary ANOVA will be reported and discussed.

To assess clinical significance and intervention effectiveness, minimal clinically important difference (MCID) and minimal detectable change (MDC) will be calculated at a 95% confidence level. The MDC will be derived using the standard error of measurement (SEM), as defined by the following formulas [28]:

$$\begin{array}{c} \text{SEM }=\;{\text{SD}}_{\text{pre}}\;\times \;\sqrt{(\text{1}-\text{ ICC})\;} \end{array}$$

$$\begin{array}{c} {\text{MDC}}_{\%\text{9}\text{5}}\;=\;\text{1}.\text{96 }\times \sqrt{\text{2}\;\times \text{ SEM}} \end{array}$$

$$\begin{array}{c} {\text{MCID}}_{\text{RCI}}=\;\text{1}.\text{96 }\times \;{\text{SD}}_{\text{pre}}\;[\sqrt{\left(\text{2}\times (\text{1}-\text{ICC})\right)}] \end{array}$$

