The reliable change index (RCI) will be calculated to determine whether observed changes exceed measurement error. In these equations, SDpre denotes the standard deviation of pre-test scores in the training group, and ICC denotes the intraclass correlation coefficient (test-retest reliability). MCID_RCI_ will be used to determine the minimum clinically significant change. Reliability coefficients from previously reported studies in comparable populations will be used.

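### The MDC95 formula has SEM inside the square root, and the formula labelled MCID_RCI is the correct MDC95, so it cannot define a clinically important change

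*Protocol article*

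**What the plan says.** The last part of Statistical methods in the protocol article sets out the purpose of two thresholds: "To assess clinical significance and intervention effectiveness, minimal clinically important difference (MCID) and minimal detectable change (MDC) will be calculated at a 95% confidence level". It continues: "The MDC will be derived using the standard error of measurement (SEM), as defined by the following formulas". Three formulas follow:

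- SEM = SDpre × √(1 − ICC)
- MDC95 = 1.96 × √(2 × SEM), with the root sign covering both the 2 and the SEM
- MCID_RCI = 1.96 × SDpre × √(2 × (1 − ICC))

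The text after the formulas states: "The reliable change index (RCI) will be calculated to determine whether observed changes exceed measurement error". It then says that MCID_RCI "will be used to determine the minimum clinically significant change". On the inputs it says that "SDpre denotes the standard deviation of pre-test scores in the training group", and for the ICC: "Reliability coefficients from previously reported studies in comparable populations will be used". No numerical SD, ICC, MDC or MCID appears in the article.

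**The concern.** There are two separate faults.

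The first is arithmetic. SEM is in the unit of the outcome (degrees for landing angles, a force unit for strength). A minimal detectable change must be in that same unit, because it is compared with an observed change. The printed MDC95 carries the square root of the unit, so it cannot be compared with a change, and its value shifts when the same data are expressed in another unit.

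The second is labelling. MCID_RCI contains only the baseline SD and the test-retest reliability. It says how large a change must be to stand clear of measurement noise, and nothing about how large a change must be to matter. The article itself ties the RCI to measurement error and then gives MCID_RCI the task of marking clinical significance.

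At stake is the interpretation of results. A reported MDC could be far from the true 95% limit, and a change that is merely detectable could be reported as clinically important.

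**Working it through.** **Inputs.** The three formulas come from Statistical methods. The article gives no SD or ICC, so every numerical value below is an assumption used to show size. There is no stated MDC or MCID figure to reproduce.

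**Step 1: the correct MDC95.** The difference between two measurements, each with error SD equal to SEM, has error SD √(SEM² + SEM²) = √2 × SEM. The 95% limit is therefore 1.96 × √2 × SEM.

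**Step 2: size of the error.** Printed / correct = [1.96 × √2 × √SEM] / [1.96 × √2 × SEM] = 1/√SEM. The two agree only when SEM is exactly 1 unit.

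The last column is the chance that an athlete with no true change exceeds the printed limit, assuming normal errors. It is 2 × [1 − Φ(1.96/√SEM)], where 5% is intended.

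| Assumed SD, ICC | SEM | Printed MDC95 | Correct MDC95 | Printed / correct | Stable athlete exceeds printed limit |
|---|---|---|---|---|---|
| 4°, 0.80 | 1.789 | 3.71 | 4.96 | 0.75 | 14% |
| 5°, 0.80 | 2.236 | 4.14 | 6.20 | 0.67 | 19% |
| 6°, 0.80 | 2.683 | 4.54 | 7.44 | 0.61 | 23% |
| 2°, 0.95 | 0.447 | 1.85 | 1.24 | 1.50 | 0.3% |

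First row in full: SEM = 4 × √0.20 = 1.789. Printed: 1.96 × √(2 × 1.789) = 1.96 × 1.892 = 3.71. Correct: 1.96 × 1.414 × 1.789 = 4.96.

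Over a wider assumed grid (SD 1 to 10, ICC 0.60 to 0.95) the ratio runs from 0.40 (SD 10, ICC 0.60: 6.97 against 17.53) to 2.11 (SD 1, ICC 0.95: 1.31 against 0.62).

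**Step 3: dependence on the unit.** Take SD 5° and ICC 0.80. The printed formula gives 4.14 when worked in degrees. Worked in radians and converted back, it gives 31.4°. The correct formula gives 6.20° both ways. A force example, for illustration only because the article states no strength unit: SD 40 N and ICC 0.90 give SEM = 40 × √0.10 = 12.65 N. The printed formula gives 9.9 N worked in newtons, and 3.148 kgf = 30.9 N worked in kilogram-force. The correct value is 35.1 N either way.

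**Step 4: what MCID_RCI is.** Substituting the article's own SEM:

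1.96 × SDpre × √(2(1 − ICC)) = 1.96 × √2 × [SDpre × √(1 − ICC)] = 1.96 × √2 × SEM.

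This is the correct MDC95, and the identity held in all 40 SD-ICC combinations of the grid. Once the MDC formula is corrected, MDC95 and MCID_RCI are one number under two names. As printed, MDC95 lies below MCID_RCI when SEM > 1 and above it when SEM < 1, which is an effect of the unit alone.

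**Step 5: the inputs to SEM (secondary and conditional).** SEM = SD × √(1 − ICC) holds when SD and ICC describe the same population. Here SDpre comes from the training arm of a trial whose athletes were selected for peak valgus above 12° (Screening procedures), while the ICC is imported. Suppose that 30–50% of screened athletes exceed 12°, that the ICC is 0.7–0.9 in unselected athletes, and that baseline is measured separately from screening. Selection of the top fraction leaves a share v of the screening variance (v about 0.26 at 30% and 0.36 at 50%), and the baseline SD shrinks by √(1 − ICC²(1 − v)). The extremes are √(1 − 0.81 × 0.74) ≈ 0.64 and √(1 − 0.49 × 0.64) ≈ 0.83. On these assumptions SEM for valgus would be about 17–36% too small. If the reliability samples were selected in a similar way, this shrinks or disappears.

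**The case against.** The strongest reply is that this is a small matter. The correctly structured expression stands directly below the faulty one, which suggests that a root sign was drawn too long in typesetting. The RCI subscript openly signals a distribution-based threshold, and the formulas are attributed to a cited source that cannot be consulted here. The explicit roles go to the RCI (change beyond measurement error) and to MCID_RCI (minimum clinically significant change), and MCID_RCI is numerically sound as a 95% limit given its inputs. On this view the faulty MDC drives no classification rule of its own.

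Much of this stands. A reader might infer that both thresholds are numerically wrong. They are not: one formula is wrong, and the other is right but carries the wrong name and use. A reader might also infer that athletes within measurement error will be declared clinically changed through the MDC error. The text does not establish that, because the cut-off it assigns to clinical significance is MCID_RCI. Nor does any section say that the gap between MDC and MCID will be interpreted. It is equally tempting to state flatly that SEM is understated. The article says that the ICCs will come from comparable populations, and the 12° selection acts directly only on the valgus outcome.

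The reply does not remove the point. If the root is a slip, correcting it leaves two names for one quantity and no threshold for clinical importance. If it is not, one quantity is reported as two different values. The MDC is also listed among the tools for judging clinical significance and effectiveness, so it will be calculated and reported.

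**Conclusion.** The concern holds in two parts. The printed MDC95 is wrong by a factor of 1/√SEM and depends on the unit. For the assumed valgus values it is 25% too low (SD 4°, ICC 0.80), 39% too low (SD 6°, ICC 0.80) or 50% too high (SD 2°, ICC 0.95). The algebra rests on no assumption; the sizes rest on assumed SD and ICC values. MCID_RCI is a valid reliable-change limit, identical to the correct MDC95, but it is used as a criterion of clinical significance for which the article gives no separate basis.

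The reach is limited. A reader might infer that the trial's judgement of effectiveness is compromised. The same section names the group × time interaction as the primary indicator of effectiveness, and neither that ANOVA nor the sample size uses these formulas. The error is confined to the interpretation of clinical significance. The mismatch between the SD and ICC sources is a secondary possibility for the valgus outcome, not a demonstrated bias.

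**What to change.** 1. Print MDC95 = 1.96 × √2 × SEM, with SEM outside the root.
2. Rename MCID_RCI as the reliable-change threshold and state that it is identical to MDC95, so that one value is reported.
3. Drop the claim of clinical significance based on it, or give a separately justified MCID with its source for each outcome to which it applies.
4. Optional: take SEM in outcome units directly from the reliability study. That avoids combining an SD and an ICC from different samples. Failing that, use the baseline SD pooled over both arms. Pooling makes the SD more precise but does not undo the selection above 12°, because both arms were selected in the same way.

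The cost of items 1 to 3 is one corrected equation and a few reworded sentences. Design, data collection, sample size and primary analysis stay as they are. What is lost is a label of clinical significance that the present formula cannot support.

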### Screening procedures

All potential participants will complete two screening assessments in the Sports Rehabilitation Laboratory:

*1- Tuck Jump Test with Cognitive Task:* Participants will perform continuous tuck jumps for 10 seconds while responding to visual stimuli. The test will be video-recorded and assessed for neuromuscular deficits associated with DKV [21].

*2- Single-Leg Landing Task with Cognitive Task:* Participants will perform single-leg landings from a 30-cm box while completing a visual discrimination task. Landing mechanics will be captured using 2D motion analysis techniques to quantify knee valgus angles. DKV will be defined as a peak knee valgus angle greater than 12 degrees during the single-leg landing task, consistent with established thresholds for increased ACL injury risk [22].

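### The MCID/MDC threshold takes its baseline SD from the training arm alone, which makes it needlessly imprecise; for valgus under the cognitive task it may also be too low if the borrowed ICC comes from less selected athletes

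*Protocol article*

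**What the plan says.** Statistical methods gives the threshold a purpose: "To assess clinical significance and intervention effectiveness, minimal clinically important difference (MCID) and minimal detectable change (MDC) will be calculated". MCID_RCI "will be used to determine the minimum clinically significant change", and a further sentence reads: "The reliable change index (RCI) will be calculated to determine whether observed changes exceed measurement error".

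The inputs are fixed there too. On the SD: "SDpre denotes the standard deviation of pre-test scores in the training group". On the ICC: "Reliability coefficients from previously reported studies in comparable populations will be used". No value is given for SDpre, ICC, MDC or MCID.

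Screening procedures sets the entry cut: "DKV will be defined as a peak knee valgus angle greater than 12 degrees during the single-leg landing task". That landing is done with a concurrent cognitive task. The primary objective, at the end of the Background, names peak knee valgus angle in single-leg landing under dual-task conditions, so the entry cut is on a primary measure. The same Statistical methods section makes the group × time interaction of the repeated-measures ANOVA the main indicator of effectiveness.

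**The concern.** There are two weaknesses in the inputs and one in the wording of the use. All three remain however the formulas are typeset.

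1. **SD from one arm.** MCID_RCI is proportional to SDpre, so it inherits all the sampling error of an SD from about 15 athletes, while another 15 baseline values of the same kind go unused.

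2. **SD and ICC from possibly different spreads.** SD × √(1 − ICC) recovers measurement error only if both quantities describe athletes with the same between-athlete variation. Entry above 12 degrees narrows the SD for valgus under the cognitive task. An ICC from athletes with a wider spread is too high a partner for that SD, and the product is then too small. Changes that are only measurement noise would be counted as reliable or clinically significant more often than the nominal 5%.

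3. **Role.** MCID and MDC are given a part in judging intervention effectiveness without being tied to the comparison between arms. The control arm does the same exercises without the cognitive load and may improve as well.

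**Working it through.** **Inputs from the article.** Enrolment is 30 with 1:1 allocation, so 15 per arm. The entry cut is 12 degrees. MCID_RCI = 1.96 × SDpre × √(2(1 − ICC)). **Assumed, because not in the article:** ICC 0.7 to 0.9, normal scores, and the share of source athletes passing the cut (16% to 84%). The article has no numerical threshold to reproduce. The sample size that fixes the arm size does reproduce: with f = 0.48, r = 0.5 and α = 0.05, power is 0.946 at N = 16 and 0.968 at N = 18, which agrees with the stated minimum of 18.

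**Step 1: precision of SDpre.** The 95% interval for an SD, as a multiple of the estimate, runs from √(df/χ²₀.₉₇₅) to √(df/χ²₀.₀₂₅).

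| SDpre from | df | Interval (× estimate) | Relative SE, 1/√(2 df) |
|---|---|---|---|
| training arm, n = 15 | 14 | 0.73 to 1.58 | 19% |
| pooled within arms, n = 30 | 28 | 0.79 to 1.35 | 13% |

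The same factors carry over to MCID_RCI. With 15 per arm, chance alone puts the ratio of the two arms' SDs anywhere from 0.58 to 1.73 (95% range). Under randomisation the training-arm SD and the pooled SD estimate the same quantity, so this step concerns precision only.

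**Step 2: effect of the entry cut.** Let the source athletes have SD 1 and reliability ICC, and let c be the cut in SD units from their mean. Athletes are selected when the screening score exceeds c, and the baseline is a separate measurement. With h = φ(c)/(1 − Φ(c)) and δ = h(h − c), the baseline SD among those selected is √(1 − ICC² × δ). Paired with the source ICC, this is also the ratio of computed to correct threshold.

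Worked case: source mean 10, SD 4, ICC 0.80.
- c = (12 − 10)/4 = 0.5, so 31% pass; h = 1.141, δ = 1.141 × 0.641 = 0.73.
- Ratio = √(1 − 0.64 × 0.73) = 0.73.
- Correct threshold: 1.96 × 4 × √0.4 = 4.96 degrees. Computed: 0.73 × 4.96 = 3.6 degrees.

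Ratios over the assumed range:

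| Share passing the cut | ICC 0.7 | ICC 0.8 | ICC 0.9 |
|---|---|---|---|
| 84% | 0.90 | 0.87 | 0.84 |
| 69% | 0.87 | 0.82 | 0.76 |
| 50% | 0.83 | 0.77 | 0.70 |
| 31% | 0.80 | 0.73 | 0.64 |
| 16% | 0.78 | 0.70 | 0.59 |

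Simulation with 2,000,000 athletes per ICC value agrees to within rounding.

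**Step 3: false flags.** With no true change, the two-sided rate is 2 × (1 − Φ(1.96 × ratio)). Ratios of 0.87 to 0.64 give about 9% to 21% instead of 5%; the extreme corners of the table (0.90 and 0.59) give about 8% and 25%. In the direction of improvement alone the rates are half of these. At 50% passing, for example, they are 5.2%, 6.5% and 8.6% for ICC 0.7, 0.8 and 0.9, against a nominal 2.5%.

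**Step 4: matched ICC.** In the worked case the ICC among the selected athletes is 1 − 0.20/0.73² = 0.62. Using that value, the ratio returns to 1.00. The downward bias therefore comes entirely from pairing the narrowed SD with an ICC from a wider spread.

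**The case against.** The strongest reply is that the article asks for ICCs from comparable populations. If that means athletes selected for dynamic knee valgus in a similar way, the ratio is 1.00 and nothing is understated. This stands: the source studies are not visible, so neither the existence nor the size of the bias can be settled from the document. Comparability as worded does not, however, require a matching between-athlete spread, and that is what the formula needs.

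The selection argument also has limited scope. It applies directly to valgus under the cognitive task, less to landing without the task, and not directly to EEG, EMG, balance, strength or proprioception.

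A reader might infer that the trial plans to claim effectiveness from training-arm change alone. The document does not support this. The group × time interaction is the stated main indicator, and only the SD input is restricted to one arm; nothing restricts where the threshold is applied. A reader might also infer a planned responder analysis, but the article mentions neither responders nor proportions. How the threshold is applied across arms may be set out in a fuller plan. What remains is that MCID and MDC are given an effectiveness role with no stated link to the between-arm contrast.

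Finally, pooling still leaves a fairly wide interval. That is true, but the gain costs nothing.

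**Conclusion.** The point holds as a minor one.

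- **Without outside assumptions:** taking SDpre from the training arm alone discards half the usable baseline data and widens the 95% interval for the SD, and so for MCID_RCI, from 0.79–1.35 to 0.73–1.58 times the estimate. It introduces no bias.
- **Conditionally:** for valgus under the cognitive task, the threshold would be about 0.6 to 0.9 of its correct value if the ICC comes from less selected athletes (ICC 0.7 to 0.9, 16% to 84% passing the cut, normal scores, baseline measured separately from screening). If the ICC source was selected in the same way, there is no bias. To call the threshold probably too low would go beyond what the document shows.

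Both parts affect a secondary interpretive step. The primary group × time test does not use the threshold.

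**What to change.** 1. Define SDpre as the baseline SD pooled within arms over all randomised athletes.
2. For valgus, use a published ICC only if its source reports a between-athlete SD close to this trial's baseline SD. Otherwise take a published SEM in degrees from a comparable landing task and 2D method in place of SDpre × √(1 − ICC). Name the source before analysis. A published SEM still brings in another laboratory's measurement error, so the match of task and method matters.
3. Apply the same threshold to both arms.
4. Leave statements on effectiveness to the group × time contrast, and use MCID and MDC only to help interpret its size.

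The cost is wording and a little analysis, with no new data. The downside is that the valgus threshold may come out higher, so that fewer changes count as reliable.

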## Discussion

This study aims to investigate the effects of a neuromuscular-cognitive training protocol on ACL injury-related risk factors and athletic performance in female volleyball players with DKV. By comparing the neuromuscular-cognitive training protocol with neuromuscular training alone, the study will evaluate the additional contribution of cognitive components to injury prevention strategies.

The intervention integrates motor and cognitive training under dynamic, sport-specific conditions, based on current evidence regarding neuromuscular and cognitive factors associated with injury risk. Unlike many previous injury-prevention approaches that primarily targeted isolated physical parameters, such as strength or balance, this protocol adopts a holistic strategy to enhance motor control, sensorimotor function, and cognitive performance simultaneously. This approach aims to replicate the complex and unpredictable demands of competitive volleyball, where ACL injury risk may increase, thereby addressing both biomechanical and cognitive-related risk factors.

This study investigates the integration of cognitive elements within neuromuscular training, reflecting the complex demands of competitive volleyball and potentially informing future ACL injury prevention strategies. The protocol targets female volleyball players with DKV, a high-risk yet understudied group. The randomized controlled trial design strengthens internal validity, and the intervention’s feasibility may support future implementation in sports and clinical settings. Blinded outcome assessors will be used to minimize observer bias. The study addresses the need for effective prevention programs in women’s sports amid increased participation and competitive demands.

As a study protocol, the intervention’s effectiveness remains to be determined after completion of outcome assessments. The focus on female volleyball players with DKV may limit generalizability to other populations or sports. The lack of objective biomechanical load-monitoring tools (such as GPS and accelerometry) constrains precise training intensity quantification; this limitation is partially addressed through session-RPE monitoring and standardized progression checklists, although these subjective and semi-quantitative measures cannot fully replace objective external load measures. Additionally, menstrual cycle-related variations and other physiological factors were not controlled, which may influence neuromuscular performance and intervention response in female athletes.

### Dissemination plans

Results will be disseminated through peer-reviewed journals, including open-access platforms when possible, to ensure broad accessibility for researchers, clinicians, and relevant stakeholders. A plain-language summary, accompanied by visual materials outlining key findings and practical implications, will be shared with study participants and their coaches to support the translation of research findings into sports practice.
